## 9.1 Screening Period

All consecutive patients who are of the appropriate age and who come to a participating memory clinic will be considered for the study. Some of the screening activities will be part of the clinical routine; others will be specific to this study.

During the Screening period, the investigator (or the managing physician, if the investigator and the managing physician are the same person) will provide a written description of the study and explain the study to the potential participants and their caregivers. The patient (and study partner, and/or the legal representative if applicable) will be informed that participation in the study will not prevent any currently available diagnostic option. Rather, it will give the patient the opportunity to have access to amyloid PET imaging, a diagnostic test approved by the European Medicines Agency but not yet reimbursed by most national health services.

Patients will be also informed that because of the randomisation:

- Participants assigned to the Early Amyloid PET arm will undergo amyloid PET imaging within 4 weeks after baseline and again 12 to 18 months ( $\pm 28$  days) after the first scan.
- Participants assigned to the Late Amyloid PET arm will undergo amyloid PET imaging at 8 months ( $\pm 8$  weeks) after baseline.
- For participants assigned to the Free Choice arm, the managing physician decides whether and when to order amyloid PET imaging; this imaging can be done at any time within 12 months after baseline.

During the screening visit, the investigator must ensure that all participants satisfy all the inclusion criteria listed in Section 7.3 and none of the exclusion criteria listed in Section 7.4. Waivers or protocol exceptions will not be granted prospectively by the Sponsor under any circumstances. Any exceptions to protocol-specified requirements will be considered as protocol deviations.

Signed and dated informed consent must be obtained from all participants prior to their entering the study. After the Informed Consent form is signed, the investigator will record in the participant's eCRF the results of the exams and the assessments performed by the managing physician in clinical routine since the request for diagnosis. (The investigator and the managing physician may be, but do not have to be, the same person.)

The following information will be recorded for all participants during the screening period:

- Demographics
- Personal and family medical history
- Review of current medications
- Physical examination
- Vital signs
- Height and weight
- Dementia blood workup, consisting in:
  - Complete blood cell count

- Serum electrolytes
- Glucose
- BUN/creatinine
- Serum B12 levels
- Thyroid function tests
- Liver function tests
- Evaluation of cognition/functioning (episodic memory, verbal memory, attention, verbal fluency, visual/spatial function, executive function)
- Results of brain magnetic resonance imaging (MRI) or computed tomography (CT) not older than 12 months before screening, showing the absence of an intracranial mass or other lesion(s) that might explain the cognitive impairment/complaint. Participants are eligible for the study only if these results are available.
- Managing physician's syndromic diagnosis
- The managing physician's estimate of the likelihood that the patient's symptoms are due to AD

## 9.2 Baseline Visit (V0 at T0)

The baseline visit must occur within 14 days after the screening visit. The screening visit can be combined with the baseline visit.

At the Baseline Visit (Visit 0 [V0] at Time 0 [T0]), the participants/study partners will receive a diary/questionnaire. At the Baseline visit, the results of the following will be recorded for all participants:

- Mini-Mental State Examination (MMSE®)
- EQ5D-5L (EuroQoL 5-dimension questionnaire)
- ICECAP-O (ICEpop CAPability measure for Older people)
- Brief COPE – Brief Coping Orientation to the Problems Experienced)
- Hospital Anxiety and Depression Scale (HADS)
- Managing physician's syndromic diagnosis (SCD-Plus, MCI, or dementia where Alzheimer's Disease is in the differential diagnosis)
- Maximum 4 hypotheses of etiologic diagnosis made by the managing physician, each with a diagnostic confidence (only if the diagnostic confidence >90% is not achieved for one etiologic diagnosis hypothesis)
- Diagnostic confidence (the managing physician's confidence that the diagnosis is correct) for each hypothesis.
- The managing physician's estimate of the likelihood that the patient's symptoms are due to AD.

Results of an already available neuropsychological assessment can be used at Baseline visit only if the results are not older than 6 months and based on the managing physician clinical judgement that there are no reasons to expect a change in that period.

The participants will be stratified according to the syndromic diagnosis made by the managing physician and then randomised, as described in Section [8.3.2](#).

For participants in the Early Amyloid PET arm, amyloid PET imaging will be scheduled to take place within 4 weeks after baseline. Amyloid PET will be carried out with high priority for early amyloid PET arm patients.

For participants in the Late Amyloid PET and Free Choice arm, if results of any of the following tests are available at this visit, the results will be reviewed with the participant/study partner and recorded in the eCRF:

- FDG-PET
- Lumbar puncture
- Optional blood tests
- Single photon emission computed tomography (SPECT) (specify test/s)
- Optional neuropsychiatric testing
- Other tests

### **9.3 Amyloid PET Imaging for Participants in Early Amyloid PET Arm (≤4 Weeks After Baseline)**

All female participants of childbearing potential must have a negative pregnancy test before the imaging study is done.

The participants in the Early Amyloid PET arm of the study will undergo amyloid PET imaging within 4 weeks after baseline.

If the managing physician chooses to order amyloid PET imaging for the participants in the Free Choice arm, those participants may undergo the imaging at any time from baseline to 12 months after baseline.

The following will be recorded for all participants who have undergone amyloid PET imaging:

- Amyloid PET scan results
- All AEs that occur within 48 hours of study drug administration
- All SAEs occurring within 30 days of study drug administration
- Review of concurrent medications

Amyloid PET will be carried out with high priority for early amyloid PET arm patients.

.

### **9.4 T1, 12 Weeks After Baseline**

At T1, which is defined as 12 weeks after baseline, the following will be recorded for all participants (a clinic visit is not strictly necessary at this timepoint):

- Use of medical resources, as collected in the patient questionnaire
- Syndromic diagnosis made by the managing physician

- Between Baseline and Week 12, each time a biomarker is available, the result must be communicated to the managing physician, and the etiological diagnosis as well as the diagnostic confidence must be collected immediately. This will provide a sequential collection of diagnosis and diagnostic confidence up to Week 12 visit, and all will be recorded at the Week 12 eCRF.
- Management plan made by the managing physician.
- The managing physician's estimate of the likelihood that the patient's symptoms are due to AD.

Note that amyloid PET imaging was to be performed within 4 weeks of baseline for the members of the Early Amyloid PET arm. If the managing physician chooses to order amyloid PET imaging for a member of the Free Choice arm, the imaging can be performed at any time from baseline to 12 months after baseline. At T1, the following will be recorded:

- Amyloid PET scan results
- All AEs that occurred within 48 hours of IMP administration
- All SAEs that occurred within 30 days of IMP administration

If results of any of the following tests are available at this visit, the results will be reviewed with the participant/caregiver and recorded in the eCRF:

- FDG-PET
- Lumbar puncture
- Optional blood tests
- Single photon emission computed tomography (SPECT)
- Optional neuropsychiatric testing
- Other tests

## **9.5 V1 at T2, 6 Months ( $\pm 14$ days) After Baseline**

A clinic visit (V1) is scheduled for all participants at T2, which is defined as 6 months ( $\pm 14$  days) after baseline. If the managing physician chooses to order amyloid PET imaging for a member of the Free Choice arm, the imaging may be performed at any time from baseline to 12 months after baseline.

The following will be recorded for all participants who have undergone amyloid PET imaging:

- Amyloid PET scan results
- All AEs that occurred within 48 hours of IMP administration
- All SAEs that occurred within 30 days of IMP administration

At the clinic visit at 6 months ( $\pm 14$  days) after baseline, the following will be recorded for all participants:

- A review of current medications
- Cognition/functioning (episodic memory, verbal memory, visual/spatial function, executive function)

- MMSE®
- EQ5D-5L
- ICECAP-O
- Brief COPE – Brief Coping Orientation to the Problems Experienced
- Hospital Anxiety and Depression (HAD) scale
- Use of medical resources, as collected in the patient questionnaire
- Syndromic diagnosis made by the managing physician
- Maximum 4 hypotheses of etiologic diagnosis made by the managing physician, each with a diagnostic confidence (only if the diagnostic confidence >90% is not achieved for one etiologic diagnosis hypothesis)
- Diagnostic confidence (the managing physician's confidence that the diagnosis is correct) for each hypothesis.
- Management plan made by the managing physician
- The managing physician's estimate of the likelihood that the patient's symptoms are due to AD.

If results of any of the following tests are available at this visit, the results will be reviewed with the participant/caregiver and recorded in the eCRF:

- FDG-PET
- Lumbar puncture
- Optional blood tests
- Single photon emission computed tomography (SPECT)
- Optional neuropsychiatric testing
- Other tests

## **9.6 Amyloid PET for Late Amyloid PET Arm, 8 Months ( $\pm$ 8 Weeks After Baseline)**

All female participants of childbearing potential must have a negative pregnancy test before the imaging study is done. The participants in the Late Amyloid PET arm of the study will undergo amyloid PET imaging at 8 months ( $\pm$ 8 weeks) after baseline. Amyloid PET scan must take place after the T2 visit at 6 months  $\pm$  14 days.

If the managing physician chooses to order amyloid PET imaging for the participants in the Free Choice arm, those participants may undergo the imaging at any time from baseline to 12 months after baseline.

The following will be recorded for all participants who have undergone amyloid PET imaging:

- Review of current medications
- Amyloid PET scan results
- All AEs that occurred within 48 hours of study drug administration
- All SAEs occurring within 30 days of study drug administration

## 9.7 Optional V2 at T3, 13 Months ( $\pm 4$ weeks) After Baseline

If the managing physician orders amyloid PET imaging for a member of the Free Choice arm, the imaging can be performed at any time from baseline to 12 months after baseline. At the optional V2 visit at T3, which is defined as 13 months ( $\pm 4$  weeks) after baseline, the following will be recorded for all participants who have undergone amyloid PET imaging:

- Amyloid PET scan results
- All AEs that occurred within 48 hours of IMP administration
- All SAEs that occurred within 30 days of IMP administration

At the clinic visit at T3, the following will be recorded for all participants:

- A review of current medications
- Cognition/functioning (episodic memory, verbal memory, visual/spatial function, executive function)
- MMSE
- EQ5D-5L
- ICECAP-O
- Brief COPE – Brief Coping Orientation to the Problems Experienced
- Hospital Anxiety and Depression (HAD) scale
- Use of medical resources, as collected in the patient questionnaire
- Syndromic diagnosis made by the managing physician
- Maximum 4 hypotheses of etiologic diagnosis made by the managing physician, each with a diagnostic confidence (only if the diagnostic confidence  $>90\%$  is not achieved for one etiologic diagnosis hypothesis)
- Diagnostic confidence (the managing physician's confidence that the diagnosis is correct) for each hypothesis
- Management plan made by the managing physician
- The managing physician's estimate of the likelihood that the patient's symptoms are due to AD.

If results of any of the following tests are available at this visit, the results will be reviewed with the participant/caregiver and recorded in the eCRF:

- FDG-PET
- Lumbar puncture
- Optional blood tests
- Single photon emission computed tomography (SPECT)
- Optional neuropsychiatric testing
- Other tests

## 9.8 Study Completion

Visit 2 must be completed within 13 months ( $\pm 4$  weeks) of the baseline visit. Participants who do not complete visit 2 within this period will not be replaced.

## **9.9 T4: Follow-up Visit for Participants in Early Amyloid PET Arm**

In a follow-up assessment, the participants who were randomized to the Early Amyloid PET arm will receive an optional second amyloid PET imaging scan 12 to 18 months after the first scan. All female participants of childbearing potential must have a negative pregnancy test before the imaging study is done. Concurrent medications will be reviewed before imaging.

The following will be recorded within 28 days after the optional second scan, for all participants who have undergone the second amyloid PET scan:

- Amyloid PET scan results
- All AEs that occur within 48 hours of study drug administration
- All SAEs occurring within 30 days of study drug administration

The following will be recorded for all participants in the Early Amyloid PET arm:

- Managing physician's etiologic diagnosis after review of amyloid PET imaging results
- Managing physician's management plan after review of amyloid PET imaging results

## 10 EFFICACY, SAFETY, AND OTHER VARIABLES

### 10.1 Efficacy Assessments

#### 10.1.1 Primary endpoint

The difference, at 12 weeks after baseline, between the Early Amyloid PET arm and the Late Amyloid PET arm in the proportion of patients for whom the managing physician has made an etiologic diagnosis with very high confidence ( $\geq 90\%$ ). Diagnostic confidence, which is the managing physician's confidence that the diagnosis is correct, will be measured with a VAS from 0% (no confidence) to 100% (complete confidence).

#### 10.1.2 Secondary endpoints

The timepoints are defined as follows:

- T0 = baseline,
- T1 = 12 weeks after T0,
- T2 = 6 months ( $\pm 14$  days) after T0,
- T3 = 13 months ( $\pm 4$  weeks) after T0;
- T4 =  $\leq 28$  days after the optional second scan, which will be 12 to 18 months after T0.

##### 10.1.2.1 Diagnosis and confidence

- The difference between the Early Amyloid PET arm and Late Amyloid PET arm in the time to communicate to the patient an etiologic diagnosis with very high confidence ( $\geq 90\%$ ).
- The changes in the managing physician's etiologic diagnosis at T3 vs T2 vs T1 in each arm.
- The changes in the managing physician's diagnostic confidence at T3 vs T2 vs T1 vs T0 in the Early Amyloid PET vs Late Amyloid PET arms.
- The managing physician's estimate of the likelihood that the patient's symptoms are due to AD at T3 vs T2 vs T1 vs T0 in the Early Amyloid PET arm vs the Late Amyloid PET arm.
- Changes over calendar time in the placement of amyloid PET imaging in the patient workup for participants in the Free Choice arm.

##### 10.1.2.2 Patient management

- The difference between arms (Early Amyloid PET arm, the Late Amyloid PET arm, or the Free Choice arm) in the number of patients randomised to disease-modifying drug (DMD) or any other AD clinical trial at T2.
- The difference between the Early Amyloid PET arm and the Late Amyloid PET arm in number of participants with changes in the management plan (changes in or start of a new program or pharmacologic treatment) at T1 vs T2 vs T3.

##### 10.1.2.3 Health economics

- The impact on patient-related outcomes (cognition, anxiety, depression, coping skills, and quality of life) at T3 vs T2 vs T0 in each arm

- The difference in the cost of diagnostic workup to the etiologic diagnosis with very high confidence ( $\geq 90\%$ ) in the Early Amyloid PET Imaging arm vs the Late Amyloid PET Imaging arm. (In those centres where the subjects in the Early Amyloid PET Imaging arm receive a diagnostic workup in addition to clinical evaluation before baseline, the relative costs will not be considered if the results of those exams are not known by the managing physician before the managing physician makes the etiologic diagnosis.)
- Differences in the use of medical resources (not limited to diagnostic procedures, tests, visits, and hospitalisations) and programs between Early Amyloid PET and Late Amyloid PET arms.
- The number of patients who withdraw from the study and the reasons for withdrawal.

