### 4.1.3 AMYPAD Diagnostic and Patient Management Study

To identify the optimal window of opportunity for possible intervention in the A $\beta$  pathway, researchers must establish in detail the sequence of events on the path towards AD.

This study will select and follow up a memory clinic population suspected of possible AD, focusing on those with subjective cognitive decline plus (SCD Plus), mild cognitive impairment (MCI), and dementia, to determine the utility of amyloid PET imaging with regards to change in diagnosis, diagnostic confidence, decision trees, and alterations between planned and actual patient management plans.

Through a European network of diagnostic memory clinics and affiliated PET centres, we will determine:

- Impact on diagnostic thinking and patient management
- Impact on diagnostic confidence and decision making
- Impact on patient reported outcomes
- Clinical utility of amyloid PET imaging in preclinical phases of AD (patients with SCD Plus)
- Costs and cost-effectiveness of early adoption vs late adoption of amyloid PET imaging
- Standardised methods of image quantitation across the PET tracers in order to perform pooled analysis across the AMYPAD program

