#### 5.4.1 Primary objectives

To test the hypothesis that the proportion of participants for whom the managing physician reaches an etiologic diagnosis with very high confidence ( $\geq 90\%$ ) at 12 weeks after baseline is higher for participants who underwent amyloid PET imaging shortly after baseline than for participants who have not yet undergone amyloid PET imaging (ie, participants scheduled to undergo amyloid PET imaging at 8 months [ $\pm 8$  weeks] after baseline).

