### 12.2 Populations for Analysis

**Safety Analysis Set (SAS):** All participants receiving any amount of either [F]florbetaben or [F]flutemetamol are included in the SAS.

**Full Analysis Set (FAS):** All participants randomized to the Early Amyloid PET, Late Amyloid PET, or Free Choice arm.

**Per Protocol Set (PPS):** All participants randomized to the Early Amyloid PET, Late Amyloid PET, or Free Choice arm with no major protocol deviations that would make them ineligible for the primary efficacy variable. Participants who are lost to follow-up will be excluded from the PPS.

The primary efficacy analysis will be based on the PPS population, and the secondary efficacy analysis will be based on the FAS population.

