### **12.5.3 Handling of missing values/censoring/discontinuations**

The reasons for incomplete data are many and include major protocol deviations, dropout because of study withdrawal or death, non-attendance at clinical visits, missing questionnaire items, uninterpretable images, etc.

The primary efficacy analysis will be conducted on the PPS population, which is based on complete cases.

Secondary efficacy analyses will be conducted on the FAS population. In time-to-event analyses, dropout and major protocol deviations are accounted for by censoring at the time of dropout or protocol deviation. In cross-sectional analyses and analyses of change between 2 timepoints, only complete cases will be included. Cases with a major protocol deviation before the first timepoint in the cross-sectional or change analysis will be excluded. The longitudinal mixed-effect analyses will be based on the observed cases. Data will be censored after a major protocol deviation. The underlying assumption in all analyses is that missing data are missing at random and not related to the primary outcome.

The proportion of missing data at each time point will be computed for the Early Amyloid PET, Late Amyloid PET, and Free Choice arms separately, and stratified for SCD Plus, MCI, and dementia.

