## **12.7 Sample Size Calculation**

For the primary efficacy analysis, a sample size of 300 per arm yields more than 99% power when a difference in proportion of 25% is assumed and 10% of the participants are assumed to withdraw before the end-point is reached. For difference in proportion of values of 20%, 15%, and 10%, the power is 99.6%, 93%, and 61%, respectively. For each of the three strata (SCD Plus, MCI, and dementia), a stratum sample size of 100 per arm yields 80% power when the difference is 25% and 10% of the patients withdraw before the end-point is reached.

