## **12.8 Procedures for Missing, Unused and Spurious Data**

Missing values will not be substituted by estimated values, but treated as missing in the statistical evaluation. All data from all participants dosed in the study will be included in all listings, plots, summary tables, and statistical analyses when appropriate.

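### Work-up cost up to the ≥90% confidence diagnosis has no value for patients who never reach it and no time horizon, so on the natural reading the Early versus Late cost comparison conditions on the primary outcome

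*Protocol*

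**What the plan says.** Section 10.1.2.3 of the Protocol defines the endpoint as "The difference in the cost of diagnostic workup to the etiologic diagnosis with very high confidence", Early against Late, with the threshold at 90%. The Synopsis and Section 12.6.1.3 repeat it. Sections 10.1.2.3 and 12.6.1.3 add a parenthesis on certain pre-baseline work-up costs in the Early arm. None of the three places says when cost stops accruing in a patient who never reaches the threshold.

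The general rules that could apply are these:

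- Section 12.5.3: "In cross-sectional analyses and analyses of change between 2 timepoints, only complete cases will be included".
- Section 12.5.3, on censoring: "In time-to-event analyses, dropout and major protocol deviations are accounted for by censoring at the time of dropout or protocol deviation".
- Section 12.8: "Missing values will not be substituted by estimated values, but treated as missing in the statistical evaluation".
- Section 12.2: "the secondary efficacy analysis will be based on the FAS population", the FAS being everyone randomised.

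Section 4.1.3 lists among the study's aims "Costs and cost-effectiveness of early adoption vs late adoption of amyloid PET imaging". The event that ends cost accrual is also the primary outcome. Section 5.4.1 states the hypothesis that its frequency "is higher for participants who underwent amyloid PET imaging shortly after baseline than for participants who have not yet undergone amyloid PET imaging".

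**The concern.** Cost runs until an event, and the event is the one that early PET is meant to make more frequent. A patient without the event has no defined cost. If such patients are left out, Early and Late are compared in two groups selected after randomisation on an outcome affected by the arm, and the protection of randomisation is lost for this endpoint.

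The selection need not be alike in the two arms. Late patients who reach 90% without PET may be mainly the straightforward cases, while Early patients who reach it may include harder ones. If harder cases use more tests, Early can look dearer although both arms spend the same. The tests spent on unresolved patients, which are part of what each strategy costs, do not enter this endpoint. A comparison built this way cannot carry the cost-effectiveness question that the Protocol sets itself.

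**Working it through.** **1. The plan's own figures.** Section 12.7 says that "a sample size of 300 per arm yields more than 99% power when a difference in proportion of 25% is assumed", with 10% withdrawal, and gives 99.6%, 93% and 61% for 20, 15 and 10 points. Evaluable n = 300 × 0.90 = 270 per arm. Base rates are not given, so I assume rates centred on 50%, and two-sided α = 0.05. With a continuity correction:

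power = Φ{[d − 1/n − 1.96·√(0.5/n)] / √[(p₁q₁ + p₂q₂)/n]}

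For d = 0.10: [0.1000 − 0.0037 − 0.0843] / 0.0428 = 0.28, and Φ(0.28) = 61.0%. The other differences give 92.7% (15 points), 99.6% (20) and above 99.9% (25). A stratum with n = 90 and α = 0.05/3 gives 79.9% against the stated 80%. The planning basis is reproduced. The Protocol states no figure for the cost endpoint itself.

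**2. Patients without a cost value at 12 weeks.** The excess in Late is n × d, whatever the base rate:

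- 25 points: 270 × 0.25 = 67.5, about 67 patients.
- 10 points: 270 × 0.10 = 27 patients.

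The absolute numbers do depend on the base rate. At 25 points:

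| Assumed Late / Early reaching 90% | No value, Late | No value, Early |
|---|---|---|
| 20% / 45% | 270 × 0.80 = 216 | 270 × 0.55 = 148.5 |
| 40% / 65% | 162 | 94.5 |
| 60% / 85% | 108 | 40.5 |

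**3. Illustration of the bias when true spending is equal.** All inputs here are assumed. Difficulty z is N(0,1). The mean number of tests is exp(ln 3 + 0.3z) in both arms, so the overall mean is 3·exp(0.045) = 3.14. The probability of reaching 90% falls with z on the logit scale with slope 1.0, 0.6 or 0.3, calibrated to the rates shown. Mean tests among those who reach 90%, by numerical integration:

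| Early / Late | Slope 1.0 | Slope 0.6 | Slope 0.3 |
|---|---|---|---|
| 45% / 20% | 2.72 vs 2.53 (+7.3%) | 2.85 vs 2.73 (+4.5%) | 2.99 vs 2.92 (+2.2%) |
| 65% / 40% | +6.5% | +4.3% | +2.2% |
| 85% / 60% | +6.5% | +4.3% | +2.3% |
| 30% / 20% | +3.0% | +1.8% | +0.9% |
| 50% / 40% | +2.6% | +1.7% | +0.9% |

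Early appears about 1% to 7% dearer with no true difference.

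A cruder model assumes that only easy cases (cost 1) are resolved without PET and that the additional Early diagnoses are hard cases (cost c). The mean among Early patients who reach 90% is (p_L + d·c)/(p_L + d), against 1 in Late. With c from 1.5 to 3 and p_L from 20% to 60%, Early is dearer by 0.15 to 1.11 units at 25 points and by 0.07 to 0.67 at 10 points. The size is therefore governed by the assumed link between difficulty and cost. If harder cases used fewer tests, the sign would reverse.

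**4. The same data as cost per diagnosis.** With 3.14 tests per patient in both arms and 45% against 20% diagnosed: Early 3.14/0.45 = 7.0, Late 3.14/0.20 = 15.7. The ratio is only the ratio of assumed rates, 0.45/0.20 = 2.25. It is 1.63 at 65/40 and 1.42 at 85/60. In this illustration the two summaries rank the arms in opposite order.

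**The case against.** **The restriction to patients who reach 90% is not stated.** This is correct. The complete-case sentence covers cross-sectional and change analyses, and a cost accumulated up to an event is not plainly either. A known non-event is not obviously a missing value. The nearest analogue, time to communicating the same diagnosis, is analysed by log-rank and Kaplan-Meier (12.6.1.1), which keep patients without the event. The FAS also points to everyone. But the censoring rule is given for time-to-event analyses only, and nothing extends it to cost. Leaving these patients out is an inference, though the natural one.

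**The statistical analysis plan can settle it.** It may choose an estimator and could define accrual for these patients. The end of accrual, however, is part of the endpoint as the Protocol words it in three places, so carrying these patients to a horizon would change that endpoint.

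**Resource use is a separate endpoint.** This stands. Sections 10.1.2.3 and 12.6.1.3 compare use of medical resources without regard to diagnosis. A reader might infer that unsuccessful work-up costs nothing or is never counted. The documents do not support that: it is absent from this one endpoint. The resource-use endpoint is, however, not stated as a cost and is not tied to diagnoses gained.

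**The gap may close.** Late patients are scanned at about 8 months and confidence is recorded again at the optional T3. A reader might infer that 55% of Early and 80% of Late patients are lost for good. Those shares rest on an assumed base rate and carry a 12-week planning difference into an endpoint with no time limit.

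**The illustration is thin.** It includes neither the price of PET nor the shortening of work-up once a diagnosis is reached. It shows that a bias can arise, not how large it will be. A wrong sign, or Late being 2.25 times dearer, cannot be claimed from the documents.

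**Conclusion.** The concern holds in limited form. The endpoint lacks a horizon and a value for patients who never reach 90% confidence. With the complete-case and no-substitution rules, the natural reading compares cost in groups selected on the primary outcome. The selection follows from the Protocol's own definition and hypothesis. Its extent at 12 weeks is about 67 more Late than Early patients without a value under the 25-point assumption and 27 at 10 points, assuming 270 evaluable per arm.

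The effect on the cost difference is not determined by the documents. About 1% to 7% against Early is an illustration on assumed inputs. A stronger assumed link between difficulty and cost gives more, and other assumptions could reverse it. This is a secondary endpoint with a partial safeguard in the resource-use endpoint. It should be corrected, but it does not touch the primary analysis.

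**What to change.** In 10.1.2.3 and 12.6.1.3 (and the Synopsis), define diagnostic work-up cost for every randomised Early and Late participant from T0 to a fixed horizon, whether or not 90% confidence was reached. Report it beside the proportion diagnosed at that horizon, as

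(mean cost Early − mean cost Late) / (proportion diagnosed Early − proportion diagnosed Late).

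Give it at two horizons:

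- **T2 (6 months).** Section 9.6 places the Late scan after this visit, so the comparison is in effect PET against no PET yet.
- **T3 (13 months).** The Late scan has then been done, so this is early against late adoption as in 4.1.3. Name a method for incomplete cost data, because T3 is optional. State whether an optional second Early scan that falls before T3 counts.

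Keep cost-to-diagnosis among those who reach 90% as descriptive, with the number contributing in each arm.

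No new data are needed: Table 1 and Section 10.3.14 already collect resource use at T1, T2 and T3. The price is a little more analysis, T2 figures that carry PET cost in Early only, and incomplete data at T3.
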